| Devin 2018 (RCT)        | Colorectal ca survivor (n=57)                 | HIIE promotes superior improvements and short-term maintenance of V̇O 2 peak and fat mass improvements. HIIE training at a reduced frequency also promotes maintainable cardiorespiratory fitness improvements.                                                                                                                    | -MICE-50 minutes of cycling at 50-70% peak heart rate, 3x/week -HIIE-10 minute warm up at 50-70% Hrpeak, 4 minute interval, cycling at 85-95% Hrpeak,3 minute period of active recovery, repeated 4x, total of 38 min/session -HIIT-of 2–3-weekly, 2 × 10-min series of cycling at peak power, measured with CPET prior to training,15s on-off duty cycle, 5-min warm-up, 5min cool-down | VO 2 peak
Fat mass                                                                                                                                | The research was based on pre operatively. No pre and post operative data regarding patients physical performance and quality of life |
| Bhatia C, 2019 (RCT)    | Lung ca (n=151) non-small cell lung cancer    | Short-term HIIT was feasible and safe in preoperative setting and increased cardiorespiratory fitness                                                                                                                                                                                                                                         | moderate-to-high intensity aerobic interval Exercise training -20min training 5x/week                                                                                                                                                                                                                                                                                                    | Cardiorespiratory fitness (VO 2 peak), 6MWT, oxygen saturation, leg fatigue, and dyspnea (BORG scale                                                 | This research did not mention about the usual care they practice in the control group.                                                |
| Egegaard T, 2019 (RCT)  | (n=15)                                        | High intensity was feasible, safe, and well tolerated during concomitant chemoradiotherapy; no significant differences within or between groups in any secondary outcome                                                                                                                                                                      | RT–HIIT-resistance training 70-80% 1RPM, 812reps, 2-3 sets followed with 3x3mins cycle ergometer RPE 16-18                                                                                                                                                                                                                                                                               | (VO 2 peak), functional capacity (6MWD), pulmonary function (FEV1), psychosocial parameters (quality of life (FACT-L), anxiety and depression (HADS) | - Small sample size                                                                                                                   |
| Sara Mijwell 2018 (RCT) | Breast ca who undergoing chemotherapy (n=240) | 16 weeks of resistance and HIIT was effective in preventing increases in CRF and in reducing symptom burden for patients during chemotherapy for breast cancer. These findings add to a growing body of evidence supporting the inclusion of structured exercise prescriptions, including HIIT, as a vital component of cancer rehabilitation | AT–HIIT-20 mins aerobic training at moderate intensity RPE 13-15, folloed with                                                                                                                                                                                                                                                                                                           | Piper Fatigue Scale, EORTC-QLQ-C30, and Memorial Symptom Assessment Scale.                                                                                      | The time frame of 16 weeks is quiet longer and may affect participant engagement -no physical performance test as outcome measure     |
| Dunne 2016 (RCT)        | colorectal liver metastasis (CRLM) (n=38)     | A 4-week prehabilitation programme can deliver improvements in CPET scores and QoL before liver resection. This may impact on perioperative outcome                                                                                                                                                                                           | UC-written information regarding exercise recommended by ACMS                                                                                                                                                                                                                                                                                                                            | CPET values and Quality of life (QoL) assessed using the SF36.                                                                                                  | not mentioned about the standard care delivered to the control group                                                                  |
| Banerjee 2017 (RCT)     | Bladder Ca (n=60)                             | Bladder cancer patients respond well to pre-surgical aerobic interval exercise, and the improvements in CRF                                                                                                                                                                                                                                   | Vigorous intensity aerobic interval exercise ,5–10-min warmup against light resistance 70–85% MHR                                                                                                                                                                                                                                                                                        | Cardiorespiratory fitness (VO 2 peak, AT, WRpeak), feasibility, Clavien Dindo classification, LOS                                                    | The control group did not get any exercise prior to surgery                                                                           |

Table 1: Table summarizes the RCT study of HIIT versus MICT with the gaps

In a randomised control trial study done by Devin 2018, he found that HIIT promotes superior improvements and short-term maintenance of V'O2peak and fat mass improvements in colorectal cancer survivors. In his study two groups were developed; Moderate Intensity Continuous Exercise (MICE) with consisted of 50 minutes of cycling at 50-70% peak heart rate, 3x/week and HighIntensity Interval Exercise (HIIE) consisted of 10 minutes warm-up at 50-70% of heart rate peak, 4minute interval, cycling at 85-95% of heart rate peak with 3 minute period of active recovery, repeated 4x, a total of 38 min/session (Devin et al. 2018). The result shows improvement in VO2 peak and reduction of fat mass in the high-intensity group. However, data regarding the patient's physical performance and quality of life was not recorded.

Other than that, short-term HIIT was feasible and safe in preoperative settings and increased cardiorespiratory fitness among the lung cancer population (Bhatia, 2019 ). In a study conducted by Bhatia (2019), the intervention group was given HIIT 2–3xweekly, 2 × 10-min series of cycling at peak power, measured with CPET before training, 15s on-off duty cycle, 5-min warm-up, 5-min cooldown. Cardiorespiratory fitness (VO2peak), 6MWT, oxygen saturation, leg fatigue, and dyspnea (BORG scale) had been measured. However, this research did not mention about the usual care practice in the control group.

A systematic review and meta-analysis of comparative studies on HIIT in cancer prehabilitation conducted by (Palma et al. 2020) found that HIIT has potential health benefits in patients diagnosed with cancer and is feasible and safe to perform.

In another systematic review and meta-analysis by Clifford K et al 2023, the pooled results indicated several positive associations of HIIT vs standard care with CRF or postsurgical outcomes. These findings suggest that HIIT may improve patient outcomes, with robust benefits across patient populations (Clifford et al. 2023). Preoperative HIIT shows promising results and should be included in prehabilitation programs. The high degree of heterogeneity in our analysis demonstrates differences in training programs and supports the need for further well-designed studies to improve the quality of evidence and confirm effective HIIT protocols.

One of the most difficult specialities in surgery is hepatobiliary (HPB) surgery because it requires both surgical skill and a thorough understanding of pancreatic and hepatobiliary physiology. Hepatobiliary surgery shares postoperative complications with general abdominal surgery as venous

catheter-related infection, incisional infection, pulmonary atelectasis or infection, subphrenic infection, urinary tract infection, intraperitoneal haemorrhage, and gastrointestinal tract bleeding. In a systematic review and meta-analysis by Dagorno et al. (2022), the study concluded that there was no effect of prehabilitation programs in HPB surgery was observed on LOS or postoperative complications rate. However, this study did not specifically measure the exercise prehabilitation interventions effect. But, in other research, involved 1778 titles and abstracts and selected 6 (randomized controlled trial, n = 3; prospective cohort, n = 1; retrospective cohort, n = 2) that included 957 patients. Of those, 536 patients (56.0%) underwent exercise prehabilitation and 421 (44.0%) received standard care. Patients in both groups were similar with regards to important demographic factors. Prehabilitation was associated with a 5.20-day LOS reduction ( $P = 0.03$ ); when outliers were removed, LOS reduction decreased to 1.85 days and was non-statistically significant ( $P = 0.34$ ) which described that exercise prehabilitation may reduce LOS and morbidity following HPB surgery and studies with well-defined exercise regimens are needed to optimize exercise prehabilitation outcomes (Deprato et al 2022).

Most of the research comparing HIIT and MICT was based on pre operatively only. There are no pre and post-operative data regarding patients' physical performance and quality of life. Besides that, some research did not mention about the usual care they practice in the control group (Bhatia 2019) ( Dunne 2016). While, Egegaard 2019 presents a small sample size in their research. Research done by Sara Mijwell 2018 reported the finding within the time frame of 16 weeks which is quite long and may affect participant engagement. Furthermore, the research did not measure physical performance as their outcome. While the control group did not get any exercise before surgery in research done by Banerjee 2017.

In Malaysia, there are no data regarding patient's health status such as ambulation status, performance test, and quality of life before undergoing major abdominal surgery and sequences after surgery. Besides that, there is no protocol in terms of determining the right dosage of exercise during prehabilitation phase. It is crucial to demonstrate that patients undergoing major abdominal surgery in this setting may derive benefits from a prehabilitation program. Therefore, besides the gaps of the previous studies, this study aims to evaluate the effectiveness of high-intensity interval training (HIIT)

compared to moderate intensity continuous training (MICT) in prehabilitation among patients undergoing major abdominal surgery in our setting and the sequences of the effect after operation.

## **1.2 Research Questions**

- 1.21 What is the current practice amongst physiotherapists treating patients following major abdominal surgery in Malaysia?
- 1.22. What is the optimum prehabilitation program with a focus on exercise intervention to improve multidomain recovery following major abdominal surgery in Malaysia
- 1.23 How does a change in exercise intervention protocol (HIIT versus MICT) affect multidomain recovery that includes, cardiorespiratory fitness, respiratory muscle strength, physical function, pain and discomfort, psychological recovery, and health-related quality of life (HRQOL)?
- 1.24 What are the clinimetric properties (MCID) of selected pain, function and physical activity assessment tools used following major abdominal surgery in Malaysia

## **1.3. Objectives**

### **Primary Objective**

To determine the effect of HIIT over MICT on physical performance which is cardiorespiratory fitness (6MWT) and maximum inspiratory pressure among patients undergoing major abdominal surgery.

### **Secondary Objectives**

- i) To assess the effect of HIIT over MICT on physical performances (Short Physical Performance Battery and 1 minute Sit to Stand), upper limb strength (Hand Grip Test) and body composition (Bioimpedance test), fatigue (Fatigue Severity Scale), psychological recovery (the Hospital Anxiety Depression Scale (HADS) and health related quality of life (EuroQoL).
- ii) To identify what is the type of exercise timing, dosing and content of prehabilitation
- iii) To determine the current practice among Malaysian physiotherapists on treating patients undergoing major abdominal surgery

- iv) To determine the clinometric properties of selected pain, function and physical activity assessment tools used following major abdominal surgery in Malaysia.

#### **1.4 Hypothesis**

- i. There will be variations in the standard of practice to these key questions across different states in Malaysia and among Malaysian physiotherapists in treating patients undergoing major abdominal surgery.
- ii. HIIT is non-inferior to MICT in improving cardiorespiratory fitness, maximum inspiratory pressure, physical performance, upper limb strength, body composition, fatigue, psychological recovery and health-related quality of life

#### **1.5 Expected Outcome and Benefit**

Findings from this study will warrant its application to every prehabilitation patient who undergoes major abdominal surgery:

- i. Aerobic training, resistance training and respiratory training might help the patient to improve physical performance and quality of life before the operation.
- ii. Prehabilitation exercise might help patients to recover faster by reducing the length of stay and reducing the rate of PPC and mortality.
- iii. The results of the present study will help physiotherapists to extend the protocol and improvise the protocol if necessary.
- iv. First RCT with robust methodology in Malaysia and worldwide
- v. the outcomes of this study inform the implementation of clinical and regulatory guidelines on prehabilitation based on the Malaysian model for patient and community safety; quality of life and standards of care of individuals scheduled for MAS surgery
- vi. This research could influence the prehabilitation protocol and exercise recommendations for abdominal surgery by emphasizing the importance of precise exercise dosage.

## **2.0 Research Methodology**

### **2.1 Study Design**

This study will be 2 phases: (i) Phase 1 will be a cross-sectional web survey will be conducted to explore the current practice amongst physiotherapists treating patients following major abdominal surgery in Malaysia hospitals and (ii) Phase 2 will be a prospective, double-blinded randomized controlled trial which aims to determine the effect of HIIT over MICT on multi-domain recovery.

#### **Phase 1: Web Survey on Current Practices**

The first phase provides critical background information. It aims to assess the current practices among physiotherapists in Malaysia regarding prehabilitation for major abdominal surgery patients. This phase helps identify the standard care approaches, frequency, type of exercises used (if any), and possible gaps in the existing practice. Understanding these current practices is essential because:

- It sets a baseline for what is already being implemented in Malaysia.
- It helps to contextualize the results of the RCT in Phase 2, as the study participants are likely to have been treated according to these existing practices.
- The data collected will inform standard care in the control arm of the RCT (moderate-intensity continuous training, MICT).

#### **Phase 2: RCT Comparing HIIT vs. MICT**

The randomized controlled trial (RCT) in Phase 2 will test the effectiveness of High-Intensity Interval Training (HIIT) compared to current standard of care (which will likely resemble the practices identified in Phase 1, i.e., MICT). This phase aims to demonstrate whether a change in the type of prehabilitation exercise improves multidomain recovery, including functional capacity, postoperative complications, and quality of life.

#### **Link Between Phases:**

Phase 1 lays the foundation for Phase 2 by providing a clearer understanding of the standard care practices that will serve as the control intervention (MICT). Without Phase 1, the RCT in Phase 2 may lack context or not fully represent the local practices in Malaysia, which may differ from international standards. Including both phases provides a comprehensive approach that not only evaluates an innovative intervention (HIIT) but also benchmarks it against real-world practices in Malaysia. In conclusion, both phases complement each other, with Phase 1 informing the setup of

Phase 2, ensuring the findings are relevant to local practice and helping to close the gap between current practice and emerging evidence-based interventions.

## **Phase 1 (Web Survey)**

A survey form using a cross-sectional, observational design will be created and distributed via an online survey tool. We will identify a tool that can house questions designed with built-in logic and direct respondents to sections of an online web survey based on their preceding answers. The online survey will then be circulated and a reminder regarding completion of the web survey will be submitted. The surveys will provide a basic analysis of raw data. Ethics approval will be obtained from the UKM and KKM ethics committee.

All Malaysian hospitals conducting general surgery will be identified. Hospitals will be contacted to establish if abdominal surgery was performed and whether the facility provided a physiotherapy service to patients undergoing abdominal surgery. The physiotherapy head of the department, Cardiovascular Pulmonary Special Interest Group (CVPG), Malaysian Physiotherapy Association (MPA) will provide further contact details and/or email addresses of physiotherapists. Once the participants who meet the inclusion criteria decide to take part in the study, they will be required to fill in the consent form in the first section of the online tools before continuing to the following section. Participants will be encouraged to forward the email to other relevant clinicians, increasing the response rate.

Before use, 10% (n=7) independent individuals will be identified to validate the survey questionnaire for readability and face validity. The participants will be physiotherapists with a particular interest and knowledge regarding major abdominal surgery and health professionals in different fields of work. The main objective is to identify any unanticipated problems and ambiguity within the instructions and questions and recognize the time commitments required to complete the survey, allowing modification before dissemination.

### **Study Period**

The study will be carried out in October 2024- October 2025.

### **Study Location**

The study will be carried out through an online survey form and distributed to the entire Malaysia.

### **Study Population**

#### **Inclusion Criteria:**

- A qualified physiotherapist who has treated patients following abdominal surgery in Malaysian hospitals.

#### **Exclusion Criteria:**

- Physiotherapists who are treating other than Cardiorespiratory patients
- Cardiorespiratory physiotherapist who is dealing with administration work with less clinical practice.

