## Data collection

A questionnaire was borrowed from Patman et al (2017), and Aldhuhoori et al (2021) a previous study with similar objectives completed in Australia and United Emirate Arabs. The questionnaire will be modified slightly based on current evidence with the consent of the origin to produce the final version. The questionnaire had 51 questions cutting across 7 sections that investigated the assessment tools and interventions and explored current practice amongst physiotherapists treating patients following abdominal surgery in Malaysia hospitals. The questionnaire will be divided into seven sections, including: i. participants' information, ii. patient demographics, iii. patient-physiotherapy factors for commencing treatment, iv prescription and v. dosage of interventions, vi. mobility prescription following abdominal surgery (frequency, intensity, and duration of mobility prescription), and vii. discharge planning.

The questionnaire will be validated to identify any problems with the English version web survey among a group of volunteers of 10% of physiotherapist from HTCM who has not treated other than cardiorespiratory patient. Following validation of the questionnaire, 74 participants will be invited and directed to questions in each section based on their preceding answers. Most of the questionnaire will be close-ended, incorporating a ranking system and matrix scale, with some open-ended questions to allow respondents to elaborate as appropriate. A link of the web survey will be distributed to potential participants and informed consent will be obtained upon their response. After two weeks, a reminder email will be resent again. Figure I the research flow chart for study 1.

Figure I

[figure not shown]

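### The Phase 1 survey excludes physiotherapists that its own inclusion criterion, objective (iii) and hypothesis (i) take in, so its results would describe cardiorespiratory physiotherapists and not Malaysian physiotherapists in general

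*Protocol*

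**What the plan says.** In the Protocol, Phase 1 (Web Survey), Study Population, there is one inclusion criterion: "A qualified physiotherapist who has treated patients following abdominal surgery in Malaysian hospitals". It carries no condition on specialty or caseload. The first exclusion criterion is "Physiotherapists who are treating other than Cardiorespiratory patients". The second is "Cardiorespiratory physiotherapist who is dealing with administration work with less clinical practice".

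The aims served by the survey are stated without a specialty limit. Secondary objective (iii) is "To determine the current practice among Malaysian physiotherapists on treating patients undergoing major abdominal surgery". Hypothesis (i) in section 1.4 expects variation in the standard of practice "across different states in Malaysia and among Malaysian physiotherapists in treating patients undergoing major abdominal surgery". Research question 1.21 and section 2.1 use the same open population. On the sampling frame, the Phase 1 section says "All Malaysian hospitals conducting general surgery will be identified", encourages recipients to forward the invitation to other relevant clinicians, and distributes the survey nationwide.

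The survey also has a role in Phase 2. Under Phase 1: Web Survey on Current Practices, the Protocol says "The data collected will inform standard care in the control arm of the RCT".

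**The concern.** Eligibility criteria define the population to which a survey's percentages apply. Here the inclusion criterion and the exclusion criterion define different populations, and the aims match only the first. Someone on a mixed or rotating caseload who treats abdominal surgery patients is let in by one rule and put out by the next.

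If the exclusion is applied as worded, caseload type (specialist against general) is removed as a source of variation before any data are collected. Hypothesis (i) is about variation among physiotherapists, so the entry rule bears directly on it. A report that then spoke of practice among Malaysian physiotherapists would claim more than the sample can carry. The same applies to the statements under Phase 1 and Link Between Phases that the survey provides a baseline of what is done in Malaysia.

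**Working it through.** **1. Applying the criteria to three kinds of physiotherapist, each of whom has treated abdominal surgery patients in a Malaysian hospital**

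| Caseload | Inclusion | First exclusion, literal reading | First exclusion, read as excluding by field |
|---|---|---|---|
| Cardiorespiratory only | met | stays | stays |
| Mixed or rotating, including cardiorespiratory | met | removed | unclear, probably stays |
| Main field not cardiorespiratory | met | removed | removed |

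All three belong to the population of objective (iii) and hypothesis (i). On the literal reading two of the three are lost. On the reading by field at least one is still lost and the middle row is left to whoever screens. Neither reading agrees with the inclusion criterion and the aims.

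**2. Which reading the rest of the Protocol favours**

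- Phase 1, Data collection describes the validators of the questionnaire as physiotherapists "who has not treated other than cardiorespiratory patient". That is the exclusive sense, but it concerns validators and not respondents.
- Phase 1, Sampling and Sample Size Calculations is built on the share of cardiorespiratory physiotherapists, which fits a specialist population.
- The second exclusion classifies people by field, which fits either reading.

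The literal reading is the plainer one, but it is not the only one.

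**3. The survey's own figures**

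Inputs from Sampling and Sample Size Calculations: z = 1.96, p = 113/19,135 = 0.0059, rounded to 0.006, and delta = 0.02.

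- n = (z/delta)² × p(1 − p) = (1.96/0.02)² × 0.006 × 0.994 = 9,604 × 0.005964 = 57.3, which matches the stated 57.
- 57 × 1.30 = 74.1, which matches the stated 74.

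The figures reproduce. They do not settle who is eligible, and correcting the criterion does not by itself change them.

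**4. Can the bias be computed?**

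Let g be the share of physiotherapists treating abdominal surgery patients who are excluded, and let S and G be the rates of some practice among those kept and those excluded. The rate in the full population is (1 − g)S + gG. The survey estimates S. The difference is

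S − [(1 − g)S + gG] = g(S − G).

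The Protocol gives neither g nor S − G. The ratio 113/19,135 is not 1 − g: its denominator is all physiotherapists, not those who treat these patients, and the Protocol does not say that the 113 are those who pass the exclusion. The bias is zero if either factor is zero, and its size is otherwise unknown.

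**5. The separate limit on comparing states**

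The Protocol gives no number of states and no split of respondents. Assuming 10 to 16 states or territories and an even spread, 57 replies give 57/10 = 5.7 down to 57/16 = 3.6 per state. For a proportion of 0.5 the 95% half-width is 1.96 × √(0.25/5.7) = 0.41 up to 1.96 × √(0.25/3.56) = 0.52, that is, 41 to 52 percentage points. Recruitment is by convenience sampling and no stratification by state is stated. This weakness remains whatever is done about the exclusion.

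**The case against.** The focus on cardiorespiratory physiotherapists may be deliberate. Contacts come partly through a cardiovascular and pulmonary interest group, the sample size is built on that specialty, and asking those most involved in the care is a defensible choice. The exclusion can also be read as one by field, which would keep a mixed-caseload physiotherapist who treats cardiorespiratory patients. The wording for validators cannot decide the matter, since the Phase 1 section and Study Method also allow validators who are health professionals in other fields.

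These points have force, but they do not remove the conflict. If specialists are intended, then objective (iii) and hypothesis (i) are worded too widely. If they are not, the exclusion is worded too tightly.

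Four stronger readings are tempting and are not supported:

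- **That the survey cannot describe practice or differences between states.** The exclusion is by caseload, not geography. Cardiorespiratory physiotherapists in different states can still be described and compared, within the limits of the sample.
- **That the eligible pool is at most 113 people**, so that 57 replies are 50% of it (57/113) and 74 are 65% (74/113). The Protocol gives 113 without source or definition and does not equate it with those who pass the criteria.
- **That the bias can be stated in percentage points.** Supposing g of 50% to 80% and a difference of 20 to 40 points would give 0.5 × 20 = 10 to 0.8 × 40 = 32 points, but nothing in the Protocol anchors either range.
- **That the control arm of the trial is compromised.** MICT is already specified in detail under Standard Care for Control Group. Invitations to the trial begin in February 2025, while the survey runs to October 2025. What suffers is mainly the claim that the comparator was benchmarked against local practice.

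**Conclusion.** The point holds as a contradiction between the Phase 1 eligibility criteria and the population named in objective (iii) and hypothesis (i). On the literal reading, physiotherapists with mixed caseloads who treat abdominal surgery patients are both included and excluded, and the results would speak for cardiorespiratory physiotherapists only. On the reading by field the restriction is milder, but it still disagrees with the aims and leaves mixed caseloads undefined.

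Its size in people or percentage points cannot be derived from the Protocol. The consequence is confined to what a descriptive secondary survey may conclude, and to the statement that it gives a baseline of local practice. The primary result of the randomised trial is not affected. It should be corrected because it decides who is surveyed or what may be claimed, and because either correction is cheap.

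**What to change.** Choose one of two routes.

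1. **Keep the national aim.** Delete the first exclusion, or reword it so that any physiotherapist who meets the inclusion criterion stays eligible whatever else is in the caseload. Record caseload type (cardiorespiratory only or mixed) and state in the participants' information section of the questionnaire, if they are not already there, and report practice overall, by caseload type and by state. The state results should be presented as descriptive, given convenience sampling and about 57 replies.
2. **Keep the specialist sample.** If specialists are intended, or collection is already complete, restate objective (iii), hypothesis (i) and the local-practice statements under Phase 1, Phase 2 and Link Between Phases as concerning practice among cardiorespiratory physiotherapists. Define whether that means exclusively or mainly cardiorespiratory.

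The first route costs one criterion and at most two questionnaire items, and gives a more mixed respondent group. The second costs wording only, and gives a narrower claim. Either needs an ethics amendment, since the approval letter requires changes to study documents to be notified and approved. The target of 74 need not change on account of this point.
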